### Outcome measures

All tests will be performed by one assessor who is blind to group allocation at baseline (< 2 weeks before the intervention start) and post treatment (within < 2 weeks after last treatment). The assessor will be trained in the testing procedures before the start of this study.

### Primary outcome measure – m-ABC-2

The primary outcome measure is the score on the m-ABC-2 (Dutch translation [30]), reflecting the fine motor skills, gross motor skills and coordination abilities.

### Secondary outcome measures

#### Motor coordination questionnaire

Parents will be asked to fill in a questionnaire about 16 motor skills before and after the intervention, the Motor Coordination Questionnaire. Prior to the start of the intervention, they are asked how well their child is at performing these motor skills (part A), and how important it is for their child to perform well on these motor skills (part B). Children are also asked to fill out this questionnaire during the first training session. Parents and children can complement the questionnaire, with motor skills that are not present on the questionnaire, but important for their child to master. The answers help to choose the motor skills that will be trained during the intervention. After the intervention, parents and children will be asked to fill out this questionnaire again, however in addition to questions focusing on how well the child is able to perform the motor skills (part A), it is asked whether they think that the child has become better or worse in performing these motor skills (part C). All answers need to be filled out on a 5-point Likert scale. The score on the Motor Coordination Questionnaire will serve as an evaluation of the perceived improvement of motor skills of both participating children and their parents.

#### Video- analysis of the trained motor skills

Because motor learning is highly task-specific, general motor tests may not fully capture the change in trained skills that have few elements in common with the test items (for instance riding a bicycle). Therefore, the two self-selected motor skills will also be video recorded at the beginning of the first training session and at the end of the last training session. An independent assessor that is blind to group allocation and the time of recording will score the critical differences in execution of these skills. These outcome parameters will be more specific to the two trained motor skills than the m-ABC-2 score. In case the trained skill is handwriting, a standardized handwriting test (SOS-2 [49, 50]) will be used to evaluate the training effect.

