
## Methods/Design

### Design

This study is a randomized controlled multicenter trial with two rehabilitation centers and 17 private practices for occupational and physical therapy across the Netherlands who are willing to co-operate. Therapists will participate in an instructive workshop about the MI or CO-OP training. MI training will be compared to CO-OP training, a recommended therapy for children with DCD. MI therapists will participate in an instructional course of 3 h, before the start of the study. CO-OP therapists have followed a two-day CO-OP training as designed by Polatajko and Mandich [29]. For the present study they will also participate in a short training of 1.5 h to update their knowledge of the CO-OP training and assure a standardized protocol. Children that meet the inclusion criteria for this study, will be randomly allocated to either the MI or CO-OP training group, see Fig. 1. Children in the MI and CO-OP group will receive the same amount therapist contact and training time as well as homework exercises.

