### Interventions

Both the MI and CO-OP intervention will be delivered for 9 weeks with 1 training session per week of 45 min. Additionally, participating children receive a homework booklet from their therapist and are required to practice 4 times a week for 10 min at home. Homework will be recorded by use of a diary. The number of 9 sessions was chosen because earlier studies on MI training in children with DCD [22] and CO-OP training [10, 15, 17] showed a training effect in the intervention group using 5 – 10 sessions. The 1 session per week was chosen as this was the most feasible schedule in both the rehabilitation centers and private practices, and has also been used in earlier studies on MI training [22]. For the CO-OP training it is not specified whether sessions should be once a week or more or less frequent [29, 33], but a recent study showing the effectiveness of a CO-OP intervention has also used sessions once a week [17]. Two self-chosen skills that are important for the child to learn will be selected for training during the 9 week intervention period [9]. The Motor Coordination Questionnaire will be filled in by both the parents and the children (guided by the therapist) to examine which motor skills are difficult for the child to perform (part A), and which motor skills are important for the child to master (part B). Using these two parts of the questionnaire, the therapist will help the child to choose two skills that will be targeted during the intervention period.

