The training protocol consists of several parts that will be run through every training session: (a) discuss homework of the past week and determine goal of current session (10 min), (b) watch videos of selected motor skill from 3^rd^ person perspective and 1^st^ person perspective, followed by mental rehearsal of this motor skill (10 min), (c) overt practice of the motor skill (10 min), (d) alternating mental rehearsal and overt practice of the motor skill, and compare and reflect on overt practice and mental rehearsal (10 min); (e) explaining homework for next week, advice for parents to motivate their child, goal of upcoming week (5 min). Videos of the following motor skills are provided by the researchers to the therapists: (a) Running and playing tag, (b) Throwing and catching a ball, (c) Hopping and playing hopscotch, (d) Jumping (amongst others rope skipping), (e) Bicycling, (f) Playing baseball, (g) Playing tennis, (h) Handwriting and (i) Eating with cutlery. On the videos the performance of the skill by a child aged 7–12 years is shown. If therapists want to train another motor skill with the child, they can record a short video themselves. Time practicing the two selected motor skills will be evenly distributed.

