### CO-OP training

Like the MI training, the CO-OP training will focus on the acquisition of two self-chosen skills that are important for the child to learn. CO-OP is expected to improve the knowledge of the task through cognitive strategy use. CO-OP approach is based on cognitive behavior modification theories, in particular the verbal self-instruction strategy developed by Meichenbaum [47]. During a CO-OP intervention, a child learns this self-instruction strategy, which enables the child to identify why the performance was not successful, and to invent and execute plans to correct his/her performance (the goal-plan-do-check strategy) [13]. It is based on the belief that when a child guides himself through a problem-solving task by talking aloud, he/she learns to regulate behaviour by learning how to identify a goal, develop a plan and evaluate the success of that plan [48]. The training protocol consists of several parts that will be run through every training session: (a) discuss homework last week and determine goal of current session (10 min), (b) practice the selected motor skill using the Goal-Plan-Do-Check framework (30 min), (c) explaining homework for next week, tips for parents to motivate their child, goal of upcoming week (5 min). Time-on-task of both selected motor skills will be evenly distributed.

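### The trained-skill videos are filmed before practice in session 1 but after practice in session 9, so the change score mixes learning with a same-session effect that may not cancel between arms

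*Protocol article*

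**What the plan says.** All of this is in the protocol article.

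- **Recording times** (Video-analysis of the trained motor skills): the two self-selected skills are "video recorded at the beginning of the first training session and at the end of the last training session". The reason given for this outcome is that a general motor test can miss change in the particular skills trained. Where handwriting is trained, a standardised handwriting test (SOS-2) is used; its timing is not stated separately.
- **Scoring** (same section): "An independent assessor that is blind to group allocation and the time of recording will score the critical differences".
- **Session frame** (Interventions): "Both the MI and CO-OP intervention will be delivered for 9 weeks with 1 training session per week of 45 min".
- **MI session content** (Motor imagery training): after 10 min on homework and goals, the child watches videos, "followed by mental rehearsal of this motor skill (10 min), (c) overt practice of the motor skill (10 min"), and then has a block described as "alternating mental rehearsal and overt practice of the motor skill, and compare and reflect on overt practice and mental rehearsal (10 min"). The last 5 min go to homework and advice for parents.
- **CO-OP session content** (CO-OP training): after the same 10 min opening, "practice the selected motor skill using the Goal-Plan-Do-Check framework (30 min"), then the same 5 min close.
- **Balance between arms** (Design): "Children in the MI and CO-OP group will receive the same amount therapist contact and training time as well as homework exercises". In both arms the time is divided evenly between the two skills.
- **Other tests** (Outcome measures): the assessor-run tests are done less than 2 weeks before the start and less than 2 weeks after the last treatment.
- **Analysis** (Statistical analysis): the groups are compared on primary and secondary outcomes.

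**The concern.** A change score measures learning only if both measurements are taken under the same conditions. Here the first recording catches the child before any training, and the second catches the child at the end of a session spent on the trained skills. The difference is learning over nine weeks plus whatever the last session does to performance on the day: warm-up, short-lived practice gain, or fatigue.

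Two things are at stake. The pre-post gain in each arm cannot be read as retained learning. And because the last session has different content in the two arms, the same-day component could differ by arm and enter the planned between-group comparison. Randomisation does not protect against this, since the difference arises after allocation. Rater blinding to arm and to time of recording removes expectation from the scoring, but it cannot remove a real difference in how the child performs when filmed.

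**Working it through.** **Step 1. Conditions at each recording.**

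| | Session 1 video | Session 9 video |
|---|---|---|
| Position in session | beginning | end |
| Same-day training before filming | none | that session's training |

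The article describes no rest period, no retention recording and no pre-practice recording in session 9. The asymmetry is specific to outcomes recorded within sessions; the m-ABC-2 and the other assessor-run tests are timed by the assessment windows around treatment.

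**Step 2. Session content by arm (minutes).**

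| Block | MI | CO-OP |
|---|---|---|
| Homework review, goal | 10 | 10 |
| Video and mental rehearsal | 10 | – |
| Overt practice | 10 | – |
| Alternating rehearsal, practice and reflection | 10 | – |
| Goal-Plan-Do-Check practice | – | 30 |
| Homework, advice to parents | 5 | 5 |
| Total | 45 | 45 |

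Both arms have 30 min directed at the skills (MI: 10 + 10 + 10). If both skills are trained that day, each gets 30/2 = 15 min. Overt practice in MI is at least 10 min and at most 10 + 10 = 20 min. In CO-OP it is at most 30 min, and less in fact, because the block includes planning and checking. Time is equal and content is not. How large the gap in overt practice is cannot be derived.

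**Step 3. What a differential would do.** The article gives no acute effect, no SD and no power figure for the video outcome, so there is no figure to reproduce. The following is an illustration.

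Inputs:
- n = 29 per arm (Sample size; calculated there for the m-ABC-2)
- two-sided α = 0.05, df = 2 × 29 − 2 = 56
- no true difference in learning
- an **assumed** between-arm differential b in the same-session effect, in SD units of the score compared

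Formulas:
- Non-centrality = b × √(n/2) = b × √14.5 = 3.808 b
- Critical t (56 df) = 2.003
- False-positive rate = probability that a non-central t exceeds 2.003 in absolute value

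| b (SD, assumed) | Non-centrality | False-positive rate |
|---|---|---|
| 0 | 0 | 5.0% |
| 0.1 | 0.38 | 6.6% |
| 0.2 | 0.76 | 11.6% |
| 0.3 | 1.14 | 20.2% |

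The normal approximation gives 6.7%, 11.9% and 20.8% for the last three rows. The smallest observed difference that would reach significance is 2.003 × √(2/29) = 0.526 SD, so a differential of 0.3 SD would be 0.3/0.526 = 57% of it.

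**The case against.** The strongest case on the other side has four parts.

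1. **The between-arm effect is assumed.** Different session content does not prove a different acute effect. Whatever is common to both arms cancels in the between-group comparison, and the false-positive rates only restate the differential that was put in. This stands. A reader might infer from the 30 min CO-OP block against the 10 min MI overt-practice block that the contrast is biased, perhaps in favour of CO-OP. The documents do not support that. Both arms have 30 min of skill-directed work split over two skills, the CO-OP block is not all execution, and the effect could be facilitation or fatigue.

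2. **The last recording may not follow practice at once.** The article says only that it comes at the end of the session, and does not place it before or after the closing 5 min. This stands but changes little: the recording still follows that day's training.

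3. **Filming at the separate baseline assessment would not work.** Under Interventions and Motor coordination questionnaire, the skills are chosen with the help of a questionnaire that the child completes in the first session. They are not yet settled at the baseline visit. This stands, and the fix keeps the first recording in session 1.

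4. **The scope is limited.** This is one secondary outcome. The m-ABC-2 is not touched. Children who train handwriting are assessed with the SOS-2, so fewer than 29 per arm may have video scores for both skills.

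None of this answers the within-arm point. The two recordings are made under different conditions by a rule that the article states, and blinded scoring does not restore comparability.

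**Conclusion.** The point holds for the within-arm change: as scheduled, the video gain combines learning with a same-session component in both arms. For the between-arm comparison, the component may fail to cancel because the preceding content differs, but this is a possibility and not a demonstrated bias. Size and direction cannot be obtained from the documents.

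The illustrative false-positive rates of about 7%, 12% and 20% rest on assumed differentials of 0.1, 0.2 and 0.3 SD, on 29 children per arm with a video score, and on a simple two-group t-test. With no differential the rate stays at 5%. The primary outcome and the sample size are unaffected. The change is worth making because this is the measure added to detect skill-specific learning, and the mismatch can be removed by moving one recording.

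**What to change.** Keep the first recording at the start of session 1, stated as after the two skills are chosen and before any practice. Make the final recording before any practice as well, in one of two ways:

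- at the start of session 9; or
- where the skill can be filmed there, at the existing post-treatment assessment.

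Apply the same rule in both arms, and state when the SOS-2 is given for children who train handwriting, so that it also falls before practice on both occasions.

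**Cost.** Filming at the start of session 9 is only a change to the filming instruction and needs no extra visit, but it omits whatever is gained in that session. Filming at the post-treatment assessment keeps that gain, but some skills may be impractical to record there. Neither option changes the sample size or the training.

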#### Motor imagery performance

In earlier studies several tasks have been used that are thought to rely on an internal model of a movement – motor imagery, action planning and rapid online control of movements. Motor imagery performance will be tested with two tasks in this study, the hand rotation task [51] and the radial visual guided pointing task [52]. These two tasks are used because they are based on distinct concepts. In the hand rotation task an on-line, real-time representation of the body position is used, also called the ‘body schema’ [53, 54]. In contrast, in the radial visual guided pointing task an internal representation of the pointing movement is used to determine how long it takes to perform the task mentally, and this representation is mainly built by repeating practice and is less based on the body schema.

#### Action planning performance

In addition, a task to measure anticipatory action planning is assessed. Action planning can be defined as the ability to take the constraints of the action task and its goal into account when first taking hold of an object [55]. Tasks that examine action planning are also thought to rely on an internal model of a movement. We will use the sword task [56, 57], that has been previously used and validated in children. This task is specifically designed to measure action planning in children.

#### Rapid online control

The online control of movements requires that the motor system predicts the future location of the moving limb using a forward internal model [6, 58]. During target-directed reaching, the nervous system must implement rapid changes in trajectory in-flight, if the movement is perturbed in some way or in the event of a visually detected change in the environment. Experimentally, the operation of these internal feedback loops has been examined in children with DCD using double-step perturbation paradigms [7, 8]. In this study, we will also examine the detection and correction of online perturbations with the double step reaching paradigm.

#### Feasibility of MI training protocol

Therapists that have provided the MI or CO-OP will be asked to share their experiences and suggestions for improvement of the training after the intervention period. In addition, we will ask the children to fill in the Enjoyment Scale after the intervention period. The Enjoyment Scale is a 5 point scale with smiley faces (0 is no fun at all; 4 is super fun) that has been developed by Jelsma et al. [59]. Using the scale, we can examine whether children enjoyed the therapy, and if this is related to the overall performance score.

### Ethical approval

The MI training study has been approved by the Committee on Research Involving Human Subjects of the region Arnhem-Nijmegen in the Netherlands (protocol number 2013/463) and will be conducted in conformance with the ‘Declaration of Helsinki’. Written informed consent for participation of the parents of the children will be obtained. The trial is registered at the Dutch trial register, www.trialregister.nl (NTR5471).

### Sample size

The smallest detectable difference (SDD 95 %), regarded as clinically relevant of the m-ABC-2 as reported in the manual is two standard scores [30]. Using the SDD 95 % as the cut off, it will be established how many of the children improved their total standard score on the m-ABC-2 in the two groups. The number of participants is based on this SDD 95 %, with a statistical power of 80 % and an α = 5 % (two-tailed). Because the main question is whether the MI training group has a greater improvement of motor abilities than the CO-OP training group after the intervention, the sample size calculation is based on the difference between the MI and CO-OP training on the m-ABC-2 change score (before and after training). Power calculations yielded a required sample size of 58 participants, 29 participants in each group.

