### Statistical analysis

Statistical methods to assess differences between groups will be ANOVA and ANCOVA analyses and Mann Whitney U tests. Between group comparisons will be made for primary and secondary outcome measures. Effect sizes (D) will be calculated to determine the practical significance of these differences. D-values greater than 0.5 indicate a moderate and values greater than 0.8 will indicate a large practical significance [60]. Potential confounders, such as age, gender and score on the ADHD questionnaire, will be included in an ANCOVA.

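### The m-ABC-2 primary outcome has two summaries and an unassigned list of tests, none named as carrying the primary conclusion, and the D labels do not line up with the two-point threshold

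*Protocol article*

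**What the plan says.** Under the primary outcome heading the Protocol article says "The primary outcome measure is the score on the m-ABC-2" and does not specify a summary such as post-treatment value, change or responder status.

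The Sample size section describes the smallest detectable difference (SDD) as "regarded as clinically relevant of the m-ABC-2 as reported in the manual is two standard scores". It applies this cut-off to individual children: "it will be established how many of the children improved their total standard score on the m-ABC-2 in the two groups". It then bases the number of participants on the SDD, states that the main question is whether MI improves motor abilities more than CO-OP, and says that "the sample size calculation is based on the difference between the MI and CO-OP training on the m-ABC-2 change score". The result is that "Power calculations yielded a required sample size of 58 participants, 29 participants in each group".

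The Statistical analysis section lists ANOVA, ANCOVA and Mann-Whitney U tests for primary and secondary outcomes together, without assigning any of them to the m-ABC-2. No test for proportions is listed. The covariates given as examples are age, gender and the ADHD questionnaire score. D is to express the practical significance of the group differences: "D-values greater than 0.5 indicate a moderate and values greater than 0.8 will indicate a large practical significance".

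**The concern.** One outcome has two summaries, and nothing ranks them. The change-score difference is the powered one, but the responder count sits beside it in the same section and is not labelled supportive. The listed tests address different quantities: Mann-Whitney compares distributions, ANOVA compares means, and ANCOVA compares adjusted means. A mean comparison and a responder comparison on the same data can give different answers, so the choice of lead result stays open until the data are seen.

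The plan also has two yardsticks for whether an m-ABC-2 difference matters: two standard scores in one section, and D above 0.5 or 0.8 in another. If these mark different points on the scale, a report could claim practical significance for a difference well short of the one on which the sample size appears to rest.

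**Working it through.** **Inputs from the Protocol article.** Two-sided alpha 5%, power 80%, 29 per group, a threshold of two standard scores, and D labels at 0.5 and 0.8.

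**Assumptions.** No SD of the change score and no responder rates are given. I assume normally distributed change scores, a true difference of two points and, for the responder shares, mean changes of 1 and 3 in the two arms.

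**1. The plan's own figure.** Without an SD, 58 cannot be reproduced directly. Solving backwards for a two-sample t-test with 29 per arm and 80% power gives d = 0.749, so the implied SD is 2 / 0.749 = 2.67. As a check, SD 2.67 with a two-point difference returns 29 per arm at power 0.80. The normal approximation gives d = (1.960 + 0.842) × √(2/29) = 0.736, or SD 2.72.

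**2. D labels in standard scores, at SD 2.67.**
- D = 0.5: 0.5 × 2.67 = 1.3 points.
- D = 0.8: 0.8 × 2.67 = 2.1 points.
- A two-point difference: 2 / 2.67 = 0.75, labelled moderate.
- Smallest observed D with p < 0.05 at 29 per arm: 2.003 × √(2/29) = 0.526, or 0.526 × 2.67 = 1.4 points.

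The moderate label therefore starts about 0.7 points below the two-point threshold, and a full two-point difference does not earn the large label.

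**3. What a test of the responder count could detect.** The share improving by at least two points is 1 − Φ((2 − mean)/SD). Power comes from exact enumeration over two Binomial(29) counts.

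| SD (assumed) | Shares, mean change 1 vs 3 | Chi-square | Fisher | t-test on means |
|---|---|---|---|---|
| 2.00 | 31% vs 69% | 85% | 77% | 96% |
| 2.67 | 35% vs 65% | 61% | 50% | 80% |
| 3.00 | 37% vs 63% | 51% | 41% | 70% |

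Only the middle row is consistent with 29 per arm for a two-point difference. The other rows show sensitivity to the missing SD. In each row the responder test has less power than the t-test.

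**4. How often the two would disagree.** In 20,000 simulated trials per scenario (scores rounded to whole points, SD 2.66, true difference two points, comparator mean change 0, 1 or 2), the t-test and an uncorrected test of responder shares differed on significance in 23% to 28% of trials.

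**5. What baseline adjustment gains.** With equal variances at baseline and follow-up and correlation r between them, the variance of the ANCOVA estimate relative to the change-score estimate is (1 − r²) / (2(1 − r)) = (1 + r)/2. That is 0.75 at r = 0.5 and 0.90 at r = 0.8 (r is assumed; none is stated). Baseline m-ABC-2 is already measured in every child.

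**The case against.** The strongest reply is that the powered comparison is identified. The Sample size section states the main question and ties the calculation to the change score. This is right. A reader might infer that the section contradicts itself by basing the number of participants first on the responder count and then on the mean change. The text does not support that: the number is said to rest on the SDD, meaning the two-point threshold, and the later sentence names the variable to which it applies.

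A reader might also infer that the trial is underpowered for its responder endpoint. That does not hold either. The count has no hypothesis, target rate or test, and 80% power is never claimed for it. The responder figures above show only what would follow if it were tested.

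Nor is D a third success rule. It describes the size of the same group differences, for secondary outcomes too. The SDD is used as an individual-level cut-off, so a group D of 0.5 that falls below it is not a strict contradiction. The band in which a difference earns the moderate label without reaching significance is narrow, about 0.50 to 0.526.

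Finally, an article may leave the detailed model to a fuller document. That excuses brevity about the model. It does not settle the status of two summaries that the article itself prints without ranking, or of two relevance scales that it leaves unreconciled.

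**Conclusion.** The concern holds in a limited form. The m-ABC-2 outcome has a powered summary (difference in change score), an unlabelled second summary (the SDD responder count) and three unassigned tests, and the article does not say which result carries the primary conclusion. Baseline m-ABC-2 does not appear among the example covariates.

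The D labels and the two-point threshold are not aligned. At the implied SD of about 2.67, D = 0.5 is about 1.3 points and two points is D = 0.75. This rests on the assumption that 58 came from a two-point difference tested by a t-test.

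The potential for divergence is material: at that SD a responder test would have 61% or 50% power against 80% for the means. These are conditional figures, not figures of the plan, and over SD 2 to 3 they run from 85% to 41%. No error in the stated sample size follows from this point.

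**What to change.** Name one primary analysis: an ANCOVA of the post-treatment m-ABC-2 total standard score adjusted for the baseline score, reported as a mean difference in standard scores with a 95% confidence interval. Label the count of children improving by the SDD as supportive. Label D as descriptive for this outcome, and do not use the 0.5 and 0.8 cut-offs to claim practical significance for the m-ABC-2.

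Give the two-point SDD as context when interpreting the confidence interval. It should not become a pass/fail rule for the observed mean difference: it is an individual-level quantity, and under a true two-point difference the observed mean would fall below two about half the time.

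The cost is a change of wording, with no extra participants or measurements. The downside is less freedom to emphasise the responder or D result.
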